### Sample size

Our design will provide 80% power to detect a 25% lower fall rate for intervention compared with the control phases (IRR=0.75), using a significant level of α at 0.05. Sample size calculations used the method described by Hemming and Taljaard^37^ with coefficients from previous studies^6 8^ and data from our partner organisations. To determine the appropriate sample size for the complete stepped-wedge design, we used the Stata function “steppedwedge”^38^ following the Hussey and Hughes approach,^39^ and conservatively assumed an intra-cluster correlation of 0.007.

The primary outcome is the falls rate (falls per 1000 bed days). Based on partner organisations’ monitoring data, we determined that 30 beds per ward for three steps and four clusters per sequence will result in 14 400 bed days in four wards for 120 days (3 months), providing >80% power.^38^,^40^ An estimated 5808 patients are expected to be admitted to the study wards during the study period.

Sample size calculations for the pre-implementation and post-implementation surveys were based on paired t-tests using survey data from our feasibility study. Assuming a SD of 0.8, the proposed sample sizes will provide 80% power to detect a mean change of 0.5 points on the Likert scale, as measured by survey questions.

### Blinding

Ward staff participants will not be blinded as they will be aware they are receiving the implementation support. It is possible that patients whose routinely collected data informs the primary outcome are blinded to their participation as implementation is at a staff level and a waiver of consent for patient participation has been granted. However, this is not rigorous enough to formally refer to patient participants as blinded.

Persons assessing falls will be blinded to the intervention periods. Data analysts will be blinded for the primary data analysis.

### Intervention

The clinical intervention to be implemented into practice is informed by a Fall Prevention Strategy which was released by the district health authority that governs the participating hospitals.^41^ The strategy emphasises tailored approaches to hospital fall prevention. It encourages interventions that centre on ensuring people at risk of falling receive individualised interventions which meet their needs and incorporate principles of comprehensive care.^42^ The strategy also advises using ward-level data to guide improvement.

Participating wards are required to establish a local project team of clinical staff to co-design and lead the implementation of tailored, multicomponent fall prevention interventions on their ward. Ward teams are required to have the written support of the relevant Director of Nursing to participate in the programme. In cases of physiotherapy, occupational therapy, dietetics, speech pathology, social work, pharmacy, podiatry, orthotics and/or diversional therapy involvement, in the project team, verbal support from their respective manager is required. This combination of ‘bottom-up’ engagement in co-design and explicit ‘top-down’ leadership advocacy is intended to motivate ward teams and support them to embed local interventions into routine practice. The selection and co-design of specific interventions is informed by each ward’s local fall incident data and the ward’s unique patient, organisational and environmental characteristics and follows the Agency for Clinical Innovation’s codesign framework.^43^ Ward teams attend workshops during the improvement science training and on the ward during the intensive implementation period where they brainstorm key causes of falls on their ward and potential management strategies (informed by staff and patient surveys, evidence updates and staff experiences). This includes consideration of the cultural and linguistic backgrounds of the patient cohorts on their ward. The ward teams work with an experienced clinical facilitator to prioritise, select and tailor interventions based on their anticipated impact and achievability. The number, timing and duration of workshops is dependent on ward needs.

During the preintervention control phases, wards continue usual care including participation in any facility-based or district-wide initiatives to support the health district’s Fall Prevention Strategy. This is appropriate as our trial is testing additional support for the implementation of tailored interventions informed by the Strategy.

### Implementation strategies

The multi-faceted implementation approach is delivered to ward staff/clinicians to support them to implement their selected tailored fall prevention interventions into their local ward. The approach involves core implementation strategies of quality improvement training, clinical facilitation, ongoing staff education and training and the enduring building and maintenance of a coalition. Details of the strategies are presented in table 2 following Proctor’s *et al*’s recommendations for reporting implementation strategies.^44^ Each core strategy may branch into or incorporate additional strategies defined as per the expert recommendations for implementing change and compilation of implementation strategies.^45^ A more detailed overview of the implementation strategies is provided in online supplemental material 3. Additional implementation strategies may be created to meet individual ward needs based on their pre-implementation needs profile and selected tailored falls prevention interventions.

**Table 2 T2:** Implementation strategies

**Core implementation strategy: training (quality improvement)** **Action:** a pre-existing **i**mprovement science training course is run by the Local Health District’s education department. Quality improvement is a system of iterative review and refinement aiming to produce positive changes to optimise local and organisational outcomes.^61^ Training topics include: using diagnostic data to inform change ideas; assessing and implementing change ideas’ via Plan-Do-See-Act cycles and assessing, spreading and sustaining improvement. The course will use mixed modes of training, including presentations, workshops and interactive activities. The course will have 2 hours of additional hospital fall prevention evidence summary content added for the trial. **Justification:** research suggests quality improvement training is acceptable and feasible in supporting the implementation of multicomponent fall prevention interventions.^21 62^ Face-to-face training is perceived to be more beneficial than online training.^21^				
**Actor**	**Target(s**)	**Temporality**	**Dose**	**Outcome**
Training run by clinicians who are experts in quality improvement and fall prevention. The primary trainer is an Educator working for the health district’s education department.	A minimum of two clinicians from each participating ward who will be leading their team’s implementation of multicomponent fall prevention interventions.	Staff attend the course within the 2 week period prior to the commencement of the intensive clinical facilitation support.	Once-off, 2 day face-to-face course.	Adoption, reach, dose, sustainability.
**Core implementation strategy: facilitation** **Action**: a clinical facilitator provides ongoing training and support to clinical staff on improvement science methodology following their 2 day training course. Clinical facilitation is underpinned by theoretical models of behaviour change and involves an experienced clinician providing mentorship, guidance and support to clinical teams. Training and education may include topics such as using available data to inform and evaluate change; practical understanding of how to adapt ways of working to reflect their distinct ward/area setting, work culture, patient cohort and specific local challenges and implementing and managing change. The clinical facilitator can also provide the tailored ongoing fall prevention education and training described in the core implementation strategy below.^63^ **Justification:** clinical facilitation was successfully used to support multicomponent fall prevention intervention in a multi-site quality improvement project.^62^ The team’s prior research informing this study found clinical facilitation is acceptable and feasible in supporting the implementation of multicomponent fall prevention interventions.^23^				
**Actor**	**Target(s**)	**Temporality**	**Dose**	**Outcome**
The clinical facilitator is a full-time, trial-funded position filled by a senior Nurse Specialist. Their workload is distributed across the four participating wards at a time.	Staff on participating wards implementing multi-component fall prevention interventions.	Clinical facilitation commences in week one of the participating wards’ 17 week intensive implementation support period.	The clinical facilitator will meet face-to-face with the participating teams for at least 30 min, once a week during the 17 week intensive implementation period and is available for access at other times on an as-needs basis. Teams then move to a minimum of 4 months of 30 mins clinical facilitation per month (with additional support on request).	Adoption, reach, dose, fidelity, sustainability.
**Core implementation strategy: ongoing education and training** **Action:** tailored education about risks for and consequences of falling in hospital and training sessions on the practical delivery of ward-selected fall prevention strategies. Using adult learning techniques, staff education and training can increase staff engagement, skills, efficacy, confidence and motivation.^64 65^ **Justification:** staff education and training is an integral component of the delivery of effective fall prevention interventions in large trials in hospital settings.^9 66^ It was identified as a facilitator to multicomponent fall prevention in the team’s prior research informing this study.^18 21^				
**Actor**	**Target(s**)	**Temporality**	**Dose**	**Outcome**
Sessions are run by physiotherapy and nursing members of the study team experienced in hospital fall prevention and by the clinical facilitator.	Staff on participating wards implementing multi-component fall prevention interventions.	Education and training sessions occur during the intensive implementation phase.	The specific content, number and timing of sessions is informed by ward staff needs and preferences identified in the staff pre-implementation surveys, in discussion with ward staff and in testing their selected small local changes.	Adoption, reach, dose, fidelity.
**Core implementation strategy: build a coalition** **Action**: internal and external stakeholders are engaged to optimise the implementation effort. Justification: the research team’s relationships with broad stakeholder groups were crucial to the work informing this study.^18 21^ The implementation science field identifies a need for stakeholder engagement to optimise research and healthcare delivery.^67^				
**Actor**	**Target(s**)	**Temporality**	**Dose**	**Outcome**
The research team intentionally maps and engages stakeholders.	Internal and external stakeholders who will be involved, influence and/or impact the intervention and implementation strategies. Cohorts include but are not limited to academics, health executives and managers, clinicians, hospital staff, patients and families.	Commenced in months prior to study and in previous work informing the study. Continues throughout and after the study period.	The specific mode, number and timing of stakeholder interactions is dependent on stakeholder capacity and project needs.	Adoption, reach, dose, fidelity, sustainability.

### Outcomes

#### Primary effectiveness outcome

##### Rate of falls

Routinely collected data from the wards will be used to compare fall rates in intervention versus control periods, expressed as falls per 1000 patient bed days. The accepted definition of a fall as an unintended event where the participant comes to rest on the ground, floor or lower level, as a result of a loss of balance will be used.^46 47^ Near misses will not be included. Data will be extracted from an incident management system (where ward staff are mandated to report all falls and near misses) and coded hospital datasets from medical records to increase the validity of this measure. Falls will be adjudicated by staff masked to intervention timing.

### Secondary effectiveness outcomes

#### Rate of injurious falls and unwitnessed falls

Data on injuries associated with falls and unwitnessed falls will be extracted from hospital records and incident reports and adjudicated by staff masked to intervention period. Data will be extracted on (a) Documented injury, (b) Serious injury (harm score 1–2, eg, fractures, intracranial injuries) and (c) Falls that were not witnessed by a staff member. Data will be reported as the rate of injurious falls and the rate of unwitnessed falls per 1000 patient bed days.

#### Incidence of hospital-acquired delirium and hospital-acquired pressure injuries

Data on hospital-acquired delirium and pressure injuries will be extracted from hospital records and incident reports. Multicomponent, tailored interventions such as those delivered in this trial may improve the care for older people in hospital more broadly, which may be reflected in these related outcomes.

#### Patient length of stay

Data on patient length of stay on participating wards will be extracted from hospital records to monitor that the intervention is not associated with increased length of stay.

#### Staff professional fulfilment

Data on staff professional fulfilment will be collected via staff surveys and qualitative interviews informed by validated tools.

#### Patient mobility patterns

This will be informed by a staff survey question 4 months postintervention implementation and by qualitative data from staff and patient semi-structured interviews.

### Implementation outcomes and determinants

Implementation outcomes and determinants will be collected for the tailored fall prevention interventions as well as the implementation strategies. These are outlined in table 3 below, which also summarises the evaluation methods. Methods include quantitative surveys and qualitative interviews with key stakeholders to guide lasting implementation and scale-up,^46 48 49^ as well as address questions about barriers to and facilitators of the approach. Observations on wards, file audits and analysis of study records will also be used. Study records include field notes from study staff documenting timing, attendance and notable moods, dynamics and reflections of meetings and education sessions with participating wards. These measures have been informed by McKay’s implementation framework.^49^

**Table 3 T3:** Overview of implementation measures

	Implementation of tailored ward-based fall prevention interventions	Measurement tool	Delivery of multi-faceted implementation strategy	Measurement tool
Implementation outcomes				
Adoption	Proportion and representativeness of participating ward staff that deliver tailored fall prevention intervention.	Ward-specific audits. Staff surveys.	Proportion and representativeness of the sites that use implementation strategies.	Study records. Staff surveys.
Reach	Proportion of patients provided with fall prevention interventions.	Ward-specific audits. Staff surveys. Patient surveys and interviews.	Proportion of eligible wards who submitted EOIs.	Study records.
Dose	Extent of delivery of selected intervention components.	Ward-specific audits. Staff surveys and interviews. Patient surveys and interviews.	Hours per clinical team of delivered multi-faceted implementation strategies.	Study records/fieldwork notes.
Fidelity	Extent to which selected fall prevention interventions are implemented.	Staff surveys and interviews.	Proportion of intended training, education and facilitation sessions provided to and attended by participating clinical teams.	Study records.
Sustainability	Intended ongoing delivery of fall prevention interventions after the 4-month clinical facilitation period.	Staff surveys and interviews.	Participation in peer support sessions after clinical facilitation period has ceased. Intended use of quality improvement skills in future work.	Study records. Staff surveys.
Implementation determinants				
Acceptability	Patient and staff views of interventions’ acceptability.	Staff surveys and interviews. Patient surveys and interviews.	Staff and manager impressions of the acceptability of the implementation strategies.	Staff surveys and interviews.
Feasibility	Perceptions among the delivery team that the intervention can be successfully used or carried out within the given setting.	Study records.	Perceptions among the delivery team that the implementation strategies can be successfully used or carried out within the given setting.	Study records.
Self-efficacy	Clinician confidence applying tailored fall prevention interventions.	Staff surveys and interviews.	Clinician confidence applying quality improvement methods.	Staff surveys and interviews.
Appropriateness	Extent to which the tailored fall prevention interventions fit with ward needs.	Staff surveys and interviews. Patient surveys and interviews.	Extent to which the implementation strategies fit with ward needs.	Staff surveys and interviews. Study records.
Satisfaction	Staff and patients’ satisfaction with the impact of the tailored fall prevention strategies.	Staff surveys and interviews. Patient surveys and interviews.	Staff satisfaction with the impact of the tailored fall prevention strategies.	Staff surveys and interviews. Patient surveys and interviews.

EOIs, Expression of Interests.

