### Participant recruitment

#### Recruitment of participating wards

Twelve eligible inpatient hospital wards will be recruited to participate in the PROTECT Fall prevention programme and trial via an invitation to voluntarily submit an expression of interest (EOI). The EOI invitation and a participant information statement (PIS) will be circulated via e-mail by a district Fall Prevention and Management Coordinator to the Nurse Unit Managers and Clinical Nurse Educators of the wards of participating facilities. Wards have 2 weeks to decide if they wish to submit an EOI to participate. Ward teams will be provided with the opportunity to ask questions about the study by contacting the research team and by invitations to attend online drop-in information sessions.

If a ward wishes to participate in the study, they will be asked to return a completed EOI form to the study team. The returned EOIs will be screened to ensure they meet inclusion and exclusion criteria. If more than 12 EOIs are received, a selection of wards that optimise diversity of case mix and facility location will be selected. Wards that submit an EOI with a multidisciplinary team will be prioritised. The Nurse Unit Manager of eligible wards will be invited to provide informed consent for their ward to participate in the trial.

We have received a waiver of consent to collect patient outcome data (via routinely collected hospital data) for inpatients admitted to the participating wards during the data collection period.

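### In Table 3, strategy Reach is EOI submission and strategy Satisfaction refers to the fall interventions, so as labelled neither row measures its construct for the training, facilitation and education delivered

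*Protocol article*

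**What the plan says.** The section on implementation outcomes and determinants commits the trial to two parallel sets of measures: "Implementation outcomes and determinants will be collected for the tailored fall prevention interventions as well as the implementation strategies". Table 3 carries this out with one column for the fall prevention interventions and one for the delivery of the support.

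In the strategy column, Reach is "Proportion of eligible wards who submitted EOIs", taken from study records. Satisfaction is "Staff satisfaction with the impact of the tailored fall prevention strategies", with survey and interview data from both staff and patients as the tools.

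Table 2, in the section on implementation strategies, gives the outcomes by which each core strategy is to be judged. Reach is named for all four: quality improvement training, facilitation, ongoing education and coalition building. The entry for ongoing education, for example, is "Adoption, reach, dose, fidelity".

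The section on recruitment of participating wards explains what an EOI is. If a ward wants to join, "they will be asked to return a completed EOI form to the study team". Screening and the Nurse Unit Manager's consent follow. The section also says: "If more than 12 EOIs are received, a selection of wards that optimise diversity of case mix and facility location will be selected".

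**The concern.** This is a hybrid effectiveness-implementation trial, and what it tests is the support given to wards, so the strategy column of Table 3 describes the thing under test. The abstract gives the lack of rigorous measurement of implementation in earlier hospital falls trials as part of the rationale.

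The Reach entry records interest shown at recruitment, not who received training, facilitation or education. The Satisfaction entry asks about the fall interventions, which the other column already covers. If the table is followed as written, the report will carry a line headed reach of the strategies and a line headed satisfaction with them, and neither will mean what its heading says. A reader deciding whether to fund facilitators or training courses elsewhere could be misled by both.

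**Working it through.** No figure in the plan is in dispute. The check sets the cells of Table 3 beside Table 2 and the recruitment sequence.

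**Reach: timing.** The EOI is returned at ward recruitment. Table 2 places the two-day training course in the two weeks before intensive facilitation starts, facilitation from week one of the 17-week support period, and education sessions within that period. All three come after the EOI, so it cannot record whether anyone received them.

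**Reach: unit.** Table 2 sets the targets as at least two lead clinicians per ward for training, staff on participating wards for facilitation and education, and stakeholders for coalition building. The Table 3 numerator and denominator are both wards.

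**Reach: what the number can show.** Let E be the number of eligible wards and K the number that submit an EOI. The article gives neither.

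- The measure as stated is K/E.
- The share of eligible wards that can receive the support is at most 12/E, because 12 wards are enrolled.
- The difference is K/E − 12/E = (K − 12)/E. It is zero when K = 12 and positive whenever more than 12 wards apply, which is the case the selection rule provides for.
- Wards are recruited through the EOI, so among those enrolled the proportion is 12/12 = 100%. It has no variation between wards, and it is the same figure for every strategy. It therefore cannot serve as the per-strategy outcome that Table 2 lists.

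**Satisfaction: object.** The intervention-column cell concerns staff and patient satisfaction with the effect of the tailored fall interventions. The strategy-column cell concerns staff satisfaction with the same thing. Only the respondents change.

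**Satisfaction: neighbouring rows.** In the same column, Acceptability, Feasibility and Appropriateness all take the implementation strategies as their object; the Feasibility cell begins "Perceptions among the delivery team that the implementation strategies can be successfully used". The Satisfaction cell is out of line with these rows, which suggests text carried over from the other column.

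**Satisfaction: sources.** The cell is defined for staff only, yet patient sources are listed. The implementation strategies section says the support is delivered to ward staff and clinicians, so patients are not placed to rate it.

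**Related data in the same column.**

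| Row or source | What it records about the support |
|---|---|
| Adoption | sites that use the strategies, and how representative they are |
| Dose | hours delivered per clinical team |
| Fidelity | share of intended sessions provided to and attended by teams |
| Acceptability, Appropriateness | staff views of the strategies and their fit |
| Free-text and interview questions (Implementation data section) | effectiveness and suitability of the individual strategies |

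Study records also include "field notes from study staff documenting timing, attendance and notable moods", so attendance is already logged.

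**The case against.** The strongest reply is that the support is well measured even if two cells are loosely worded. Fidelity records sessions attended, Dose records hours per team, Adoption records use by sites, and Acceptability, Appropriateness and the interviews gather staff views of the strategies. The ward is also the recruited unit, so the share of eligible wards that apply is a coherent ward-level measure of how far the offer reached. The survey instruments are in a supplement that is not shown and may already ask staff how satisfied they were with the support. Table 3 is an overview in a condensed article.

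Much of this stands, and it limits the point. A reader might infer that nothing in the trial shows which strategies reached staff or were valued; the rows just listed rule that out. A reader might also infer that the EOI precedes every strategy, but Table 2 says coalition building began months before the study, so the timing argument covers training, facilitation and education only. Nor is the optional causal modelling of wards with greater uptake blocked: the statistical analysis section does not define uptake by the Reach row, and Dose and Fidelity are recorded per team. Finally, taking feasibility from study records is not an error. Those who deliver the strategies are mainly trainers, the facilitator and study-team members, and study records are a reasonable source for their perceptions.

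The reply does not rescue the two cells. Session attendance by teams is not the proportion of targeted staff reached, and Table 3 lists acceptability as a separate determinant from satisfaction. Ward uptake of an invitation is worth reporting, but it is not the outcome Table 2 assigns to each strategy.

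**Conclusion.** The point holds for two cells of Table 3. Strategy Satisfaction names the wrong object and lists sources that do not fit it. Strategy Reach is one recruitment-stage proportion that cannot differ by strategy or among the 12 enrolled wards, although Table 2 lists reach for every core strategy. As labelled, neither row measures its construct for the training, facilitation and education delivered.

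The consequence is confined to descriptive implementation results: two mislabelled lines in the report, with related information available nearby. The primary outcome, significance level and power are not touched. The conclusion rests on the wording of Tables 2 and 3 and the recruitment section. It does not claim that the surveys omit satisfaction with the support, because they cannot be seen. The definitions should be corrected before analysis; the change is inexpensive and the strategy column describes what the trial tests.

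**What to change.** Make two edits to the strategy column of Table 3.

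1. **Satisfaction.** Define it as staff satisfaction with the implementation strategies (training, facilitation and education), and remove the patient sources from that cell.
2. **Reach.** Define it as the proportion of each strategy's targeted staff who attended or received it, reported per ward and per strategy, from attendance already in study records. The denominator should be the group Table 2 targets for that strategy, not the whole ward staff by default. For training, the target is a minimum of two lead clinicians, so give the count beside the percentage. Report the EOI proportion separately as ward uptake of the invitation.

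Coalition building targets stakeholders rather than a ward's staff, so Table 3 should state what reach means for it.

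The cost is small: a count of targeted staff per ward as denominator and, if the staff survey does not already cover satisfaction with the support, one or two added items. Data collection began in October 2024. If a cluster's post-implementation survey has already closed without such an item, satisfaction there can be described only from free-text and interview answers, and the report should say so.
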